**Education**				
	7. Evidence and guideline education	Key evidence and related guidelines about why the behavior is important are summarized and links are provided to published evidence.	Information about health (5.1) and social and environmental consequences (5.2).	Provided beneath the peer-comparison graph for each of the quality indicators. Links to web-hosted publicly available resources. Accessible at any time after dashboard access is given.
	8. Tutorial videos	Evidence reviewed and practice from a center of excellence presented by an expert in the field. Operative video tutorials for practical skills provided. The videos can be accessed at any time, and access is unsupervised. Collaborators are encouraged to review them together at departmental meeting but they may also be accessed individually.	Instruction on how to perform the behavior (4.1) and demonstration on how to perform the behavior (6.1) by a credible source (9.1).	Links to web-hosted videos provided beneath the peer-comparison graphs on the dashboard and in the feedback email. Accessible at any time after dashboard access is given.

^a^REDCap: Research Electronic Data Capture.

**Figure 3 figure3:**
[figure not shown]
Intervention and mode of delivery. QI: quality indicator.

**Figure 4 figure4:**
[figure not shown]
Intervention and design. Web-based performance feedback and education dashboard—accessible to only sites in the intervention arm during the study. Numbers in the boxes relate to the components in Table 1.

### Prospective Data Collection After Randomization

Sites will be asked to submit observational data about all consecutive eligible TURBT cases performed after they have been randomized. Sites in the feedback and education arm will only be permitted to submit cases in the prospective phase once the mid-point survey has been received. The purpose of the midpoint survey was to determine if any unprompted changes to practice or performance had been made since the site registration survey was completed and confirm that sites had disseminated the education and feedback at their site (if relevant) and assess how this had been done.

### Primary Outcomes

#### Principles

The study will use 4 coprimary outcomes. The primary outcomes are key “surgical quality indicators” or “process measures.” The outcomes were chosen through a combination of evidence, guidelines associating their performance with improved bladder cancer outcomes, expert steering group consensus, and independent external peer review. Primary outcomes were chosen to meet the following criteria: (1) They are behaviors or practices associated with the primary operation or occurring at the time of the primary operation. (2) It is possible for the surgeon to directly influence these practices. (3) They are practices recommended by professional guidelines or evidence associating them with improved outcomes. (4) They can be objectively measured through review of the standard patient record.

Coprimary outcomes were chosen because not all behaviors are applicable to all patients and no single behavior may indicate overall quality. The 4 outcomes chosen draw on experience and the outcomes used in the Scottish Quality Performance Indicator programme and work by Mariappan et al [14,15].

The intervention will be considered effective if any one of the 4 coprimary outcomes is significantly improved. “Eligible cases” and excluded cases were determined for each coprimary outcome. Eligible cases (after exclusions) make up the denominator for calculation of the proportion of cases achieving the outcome.

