#### Randomization

Sites will be randomized 1:1 in parallel arms when the submission of the minimum required retrospective data is complete. Sites will be randomized to either (1) no intervention (the site continues to submit data on consecutive eligible cases but without performance feedback and education during the study). Once the study is complete, these sites will be provided with performance and education feedback or (2) audit, feedback, and education (performance feedback and education provided before beginning further prospective phase of study).

Sites will be randomized using the randomization app at the Centre for Healthcare Randomised Trials (CHaRT), University of Aberdeen, which developed the randomization sequence. This randomization app is available 24 hours a day, 7 days a week as a web-based app. Randomization will be minimized for site-level variables that are thought to significantly impact achievement of TURBT quality indicators. There is no blocking. These are baseline performance from the baseline audit, geographical region (continent, except that the United Kingdom is considered alone, Australia will be combined with mainland Europe), and the presence of an existing TURBT audit at that site before the study. In addition, a random component is used in the minimization algorithm to ensure concealment of the allocation.

The study administrator will access the web-based system. They will enter the minimization variables into the web-based system, which returns the allocation status. The chief investigator of the site will be informed of their allocation following randomization. There is no blinding. To prevent contamination following randomization, sites randomized to no intervention will not be granted access to the dedicated personalized feedback and education resources, which are username and password protected.

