### Sample Size

The intervention will be delivered to centers, and so the primary outcomes will also be measured at the center level. The only published data about intersite achievement of the listed coprimary outcomes are the Scottish Quality Performance Indicator programme covering 11 sites in Scotland. The outcome with the largest SD (SI-IVC) was used to determine the overall sample size. With mean 0.651 (SD 0.2) for SI-IVC, recruiting 172 sites (86 per arm) would give 90% power to detect a difference of 0.1 between the intervention and control groups at the 5% significance level. Where a smaller SD of 0.1 (detrusor muscle in specimen) or 0.15 (resection documenting) can be assumed, this would provide 90% power at the 5% significance level to detect differences of 0.05 and 0.075, respectively. It is possible that some sites may have missing data for 1 or more of the coprimary outcomes. Missing data will not be imputed for the primary outcomes. In that case, the site will be excluded from the analysis for that outcome. A sensitivity analysis will be performed to determine the effect of missing data in that outcome. An extensive international marketing campaign will be undertaken to ensure sample size is reached, along with endorsement of the study by the British Association of Urological Surgeons to all urology centers in the United Kingdom.

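### An any-one-of-four success rule is paired with sample sizing at an unsplit 5% level and no stated multiplicity control, so the false-claim rate and the stated 90% power per outcome cannot both stand.

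*Protocol article*

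**What the plan says.** Under Primary Outcomes, Principles, the article states: "The study will use 4 coprimary outcomes". It then defines success: "The intervention will be considered effective if any one of the 4 coprimary outcomes is significantly improved".

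The Sample Size section bases the size on the outcome with the largest SD, single-instillation chemotherapy (SI-IVC), with an SD of 0.2. The total is 172 sites, split equally into two arms of 86, and the claim made for this number is that it "would give 90% power to detect a difference of 0.1 between the intervention and control groups at the 5% significance level". For detrusor muscle (SD 0.1) and for completeness of resection (SD 0.15), the same section claims that "this would provide 90% power at the 5% significance level to detect differences of 0.05 and 0.075, respectively". It gives no SD or difference for the fourth indicator, documentation of tumor features.

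The Analysis section models each of the four outcomes separately at site level, with fixed effects for arm, pre-existing audit and baseline achievement, and a random effect for region. Neither that section nor the other two mentions a division of the 5%, a testing order or an adjusted threshold, and the Analysis section gives no test level.

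**The concern.** Despite the label coprimary, the rule is a union rule: one success among four is enough. Testing each endpoint at the full 5% is safe when all endpoints must succeed, because a false overall claim then needs every test to err. Under an any-of-four rule a single chance result is enough, so the 5% has to be shared.

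At stake is the trial's main conclusion, whether audit, feedback and education is effective. Its error rate is not controlled by anything the article states. If control is added later, the power in the Sample Size section no longer describes the trial.

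**Working it through.** **Inputs.** Four primary outcomes and the any-one rule (Principles). SDs of 0.2, 0.1 and 0.15, differences of 0.1, 0.05 and 0.075, 86 sites per arm, 5% level, 90% power (Sample Size). 1:1 allocation (Randomization). The article does not say whether tests are one- or two-sided, and it gives no correlations between outcomes. Those used below are assumptions.

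**Step 1: reproduce the stated size.** All three differences are 0.5 SD (0.1/0.2 = 0.05/0.1 = 0.075/0.15). The normal approximation at two-sided 5% gives n per arm = 2(1.960 + 1.282)²/0.5² = 84.1, so 85. With the noncentral t distribution, 85 per arm just misses 90% (89.99%) and 86 gives 90.3%. That matches the stated 86 exactly. A one-sided 5% test would need only 69 per arm. The size therefore rests on an unsplit two-sided 5%.

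**Step 2: error of the any-of-four rule, if each outcome is tested at two-sided 5% and there is no true effect.**
- Any p<0.05 in either direction, independent outcomes: 1 − 0.95⁴ = 18.5%.
- False improvement only, which is what the rule rewards: 1 − 0.975⁴ = 9.6%, against 2.5% for one outcome.

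With a common correlation between the four test statistics (1,000,000 simulated draws each):

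| Assumed correlation | Any p<0.05 | False improvement |
|---|---|---|
| 0 | 18.5% | 9.6% |
| 0.2 | 18.0% | 9.1% |
| 0.5 | 15.6% | 7.8% |
| 0.7 | 13.0% | 6.5% |
| 0.9 | 9.4% | 4.7% |

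**Step 3: power per outcome once the error is controlled.** The first Holm step, like Bonferroni, uses 0.05/4 = 0.0125. The noncentrality at 86 per arm is 0.5 × √(86/2) = 3.279.
- Normal approximation: Φ(3.279 − 2.498) = 78.3%.
- Noncentral t: 77.4%.
- Differences detectable with 90% power at 86 per arm, by t: 0.116, 0.058 and 0.087, in place of 0.1, 0.05 and 0.075.
- Sites needed to restore 90%, by t: 116 per arm (232 in all).

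**Step 4: what would raise the 77%.**
- Baseline adjustment multiplies the residual SD by √(1 − r²). At r = 0.4 the SD of 0.2 becomes 0.183 and power is about 85%. At r = 0.5 it becomes 0.173 and power is about 89%.
- With 110 independent clusters per arm and no baseline adjustment, power is about 88%.
- If all four outcomes truly shift by 0.5 SD, the chance that at least one passes 0.0125 at 86 per arm is 99.8% at correlation 0, 96% at 0.5 and about 91% at 0.8. If only one shifts, it is about 78%.

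**The case against.** Several points on the other side are fair.

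**The test level is inferred.** A reader might take it as fact that each outcome will be tested at 5%. The article gives 5% only in the sample-size calculation and does not define what counts as significant. A multiplicity procedure may stand in an analysis plan that is not shown. This limits the wording, but it does not remove the point: if such a procedure exists, the stated 172 sites and 90% power were not calculated for it.

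**The inflation is not simply fourfold.** A reader might infer that false claims are about four times as frequent as intended. That needs near independence (18.5/5 = 3.7; 9.6/2.5 = 3.85). Two of the indicators are read from the same operation note, so some positive correlation is plausible. At 0.5 the ratio is about 3.1. In addition, 18.5% counts significant harm as well, which the rule would not call success. The 9.6% ceiling is the relevant figure.

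**The trial is not shown to be underpowered for its own rule.** A reader might infer that the 90% fails altogether. What fails is power per outcome, which is how the Sample Size section expresses it. The chance of at least one success stays at about 91% or more for correlations up to 0.8 if all four indicators shift by 0.5 SD. The planned baseline adjustment would also help, although the article takes no credit for it and gives no correlation.

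**Accrual is above target.** The Abstract reports 220 hospitals. If each were its own cluster this would give 110 per arm, but the Study Design section lets a cluster hold several hospitals.

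None of the last three points controls the error of the success claim.

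**Conclusion.** The point holds in this form: the success rule and the sizing level, both fixed in the article, do not fit together. Either the claim of effectiveness carries a false-improvement risk of up to about 9.6% against a nominal 2.5%, or the stated 90% power per outcome is not delivered at 86 sites per arm.

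The first figure assumes two-sided 5% tests, no true effect on any indicator and independent outcomes. The excess shrinks with positive correlation but is still present at 0.9. The second assumes the article's SDs, 86 analysed sites per arm and no baseline adjustment. On those terms about 77% is the lower bound for a single outcome under Holm, not the expected power of the trial as a whole. The finding covers the three outcomes that the article sizes. It gives no figures from which power for the tumor-feature indicator could be checked.

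**What to change.** Keep the any-of-four rule and add the control it needs:

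1. In Principles and Analysis, state that Holm's procedure is applied to the four p values at an overall two-sided 5%, and that improvement is claimed only for indicators that survive. Holm is valid under any correlation between the outcomes. If an adjustment already stands in the analysis plan, state that one here.
2. In Sample Size, restate the power at 86 sites per arm as about 77% per outcome at the first Holm step without baseline adjustment, with 90%-power detectable differences of about 0.116, 0.058 and 0.087.
3. Note there that this is a lower bound. Baseline correlations of 0.4 to 0.5 (assumed) would give about 85 to 89%, 110 independent clusters per arm about 88%, and the chance of at least one success is higher if several indicators truly improve.

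The cost is a sentence on the testing procedure, a revised power statement and a less favourable headline figure. No new data are needed. The change should be recorded before the arms are compared.

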#### Quality Performance Indicator 1: The Proportion of Eligible Cases Where Detrusor Muscle Is Present in the Surgical Specimen

##### Rationale

International evidence-based guidelines include clear recommendations related to TURBT [5,7]. There is evidence that resection of detrusor muscle at the index TURBT is associated with reduced early recurrence rate [6,22] and long-term mortality [25] and is more likely to be resected by experienced than inexperienced surgeons [6,22]. If detrusor muscle is not obtained, it is not possible to accurately determine the tumor stage and all of the tumor may not have been removed, which may lead to recurrence. It is accepted that detrusor muscle resection is not appropriate in all patients and is a clinical judgment. Therefore, the average rate of detrusor muscle will be used as a performance indicator.

##### Eligibility

All cases where the tumor maximal diameter is estimated at >5 mm by the operating surgeon.

##### Assessment

The outcome will be determined from the surgical pathology report.

##### Exclusions

Where the data for the presence or absence of detrusor muscle in the specimen are investigator-missing, the case will be excluded.

#### Quality Performance Indicator 2: The Proportion of Eligible Cases Where SI-IVC Is Administered Within 24 Hours of TURBT

##### Rationale

There is high-certainty evidence supporting the use of SI-IVC, such as Mitomycin C following TURBT. It is known that SI-IVC administration can significantly reduce the rate of NMIBC recurrence [23,35-39]. EAU and AUA guidelines recommend administration of SI-IVC within 24 hours of surgery in patients most likely to benefit [5,7].

##### Eligibility

All cases at sites where it is possible to give SI-IVC.

##### Assessment

The outcome will be determined from review of the patient record.

##### Exclusions

It is anticipated that a small number of sites will be unable to provide SI-IVC due to local or national service, supply, or economic restraints. These sites will be identified from the study registration survey and excluded from this indicator a priori. Cases where a patient has a documented allergy to SI-IVC will be excluded. Where this data field is investigator-missing, the case will be excluded from this outcome.

#### Quality Performance Indicator 3: The Proportion of Eligible Cases Where Resection Completeness Is Documented in the Operation Record

##### Rationale

Guidelines strongly recommend documenting the completeness of resection [5]. Using a TURBT proforma to document the surgical procedure and findings at surgery in a standardized way is associated with improved patient outcomes [15,24,40]. Completely removing all visible tumors is a core surgical principle in cancer surgery. Documentation of this is essential for subsequent multidisciplinary team meeting decisions on the management of individual patients as it determines the need for repeat resection, which can improve oncological outcomes in selected patients [41].

##### Eligibility

All cases included in the study.

##### Assessment

The outcome will be determined from review of the operation note. To achieve the indicator, a statement that the resection was either complete, incomplete, or uncertain is required. Where there is no statement of resection completeness in the operation record the indicator will be failed.

##### Exclusions

Where this data field is investigator-missing, the case will be excluded from this outcome.

#### Quality Performance Indicator 4: The Proportion of Eligible Cases Where All of the Tumor Number, Size, and Location Are Documented in the Operation Record

##### Rationale

Guidelines strongly recommend documenting the tumor location, appearance, size, and multifocality [5]. Tumor size and number are associated with recurrence risk and are required to risk-stratify patients according to European Organisation for Research and Treatment of Cancer (EORTC) risk categories as recommended by both AUA and EAU guidelines [5,7]. Documentation of these factors and subsequent risk stratification allows multidisciplinary team meeting decisions for individual patients, determining the need for adjuvant treatments, which determine long-term oncological outcomes. Documenting tumor location also allows appropriate assessment of recurrence and resection completeness at reresection surgeries and during cystoscopic surveillance.

##### Eligibility

All cases included in the study.

##### Assessment

The outcome will be determined from review of the official operation note. To achieve the indicator, a statement of the tumor number, size (an assessment of tumor maximal diameter and at least to a resolution of <3 cm or ≥ 3 cm [a risk category cut-off in the EAU guidelines]), and location is required. Where record of any of these 3 features is missing from the operation record, the outcome will be failed.

##### Exclusions

Where this data field is investigator-missing, the case will be excluded from this outcome.

### Secondary Outcomes

#### Key Secondary Outcome: Early Recurrence Rate

##### Rationale

International guidelines recommend that a “check” cystoscopy be performed approximately 3 months after complete TURBT [5,7]. The rationale is that recurrence detected at this early stage is due to surgical failure rather than disease process [6]. Therefore, the early recurrence rate represents an outcome of surgical quality.

##### Eligibility

All cases where a cystoscopy has been performed within 6 months of complete index TURBT or planned completion re-TURBT, or, in cases where an adjuvant treatment course is given prior to check cystoscopy, at a check cystoscopy performed within 12 months.

##### Assessment

The outcome will be determined from review of the patient record. Recurrence will be defined as either (1) a clinical assessment of “highly likely” recurrence where fulguration is applied, and no surgical specimen is obtained or (2) when a surgical specimen is obtained, and then histological confirmation of cancer will be required.

##### Exclusions

Where this data field is investigator-missing. Where muscle-invasive bladder cancer is identified in either the primary or re-TURBT pathology. Where the patient is deemed not fit or appropriate for further surveillance.

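### The undated surveillance exclusion for early recurrence is either redundant or removes patients who already had the qualifying cystoscopy, and as written it permits dropping confirmed recurrences

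*Protocol article*

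**What the plan says.** All of this is in the Protocol article, mostly under Key Secondary Outcome: Early Recurrence Rate.

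- **Eligibility** requires a cystoscopy that has taken place: "All cases where a cystoscopy has been performed within 6 months of complete index TURBT or planned completion re-TURBT". After an adjuvant course the window is longer: "in cases where an adjuvant treatment course is given prior to check cystoscopy, at a check cystoscopy performed within 12 months".
- **Assessment** gives two ways to count as a recurrence. One is a clinically highly likely "recurrence where fulguration is applied, and no surgical specimen is obtained". The other applies "when a surgical specimen is obtained, and then histological confirmation of cancer will be required".
- **Exclusions** lists three reasons for removal. The first is "Where this data field is investigator-missing". The second is tied to a procedure: "Where muscle-invasive bladder cancer is identified in either the primary or re-TURBT pathology". The third is tied to nothing: "Where the patient is deemed not fit or appropriate for further surveillance".
- **Randomization** states: "There is no blinding". Under Data Management, the data come from routine records accessed by members of the clinical team.

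**The concern.** An exclusion for patients who will not be followed up normally serves to leave out people whose outcome cannot be assessed. Here Eligibility and the missing-data rule already do that. What remains for the third exclusion is mostly patients who have been assessed. The text does not say that the judgement must be made before the check cystoscopy or independently of its result.

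This opens the way to selection on a decision that can follow the outcome. A recurrence found at the check may change what happens to a patient next, and the person entering the data can see the result, the later decision and the site's allocation.

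Early recurrence enters all four items under Other Objectives: the effect of the intervention, the link with the quality indicators, the variation between surgeons and sites, and the associated factors. The covariates in the planned logistic model (tumor size, number, grade and stage, and age) cannot restore events that have been removed.

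**Working it through.** **1. Figures in the plan.** The article gives no recurrence rate and no count of patients expected to be excluded. Its only sample size concerns the coprimary outcomes. With SD 0.2, difference 0.1, 90% power and a two-sided 5% level (two-sided is assumed), the t-based solution is 85.03 per arm, rounded up to 86, or 172 sites. That agrees with the plan and does not depend on this point.

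**2. What the third exclusion can add.** The stated rules applied to possible records:

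| Record | Status before the third exclusion | Effect of the third exclusion |
|---|---|---|
| Judged unfit, no cystoscopy in the window | Not eligible | None |
| Cystoscopy done, outcome field not filled in | Removed as missing | None |
| Check cystoscopy clear, patient then leaves surveillance | Counted as no recurrence | Removed |
| Recurrence meeting the Assessment definition, patient then leaves surveillance | Counted as recurrence | Removed |
| Lesion seen, neither fulgurated nor sampled because the patient is unfit | Meets neither part of the definition | Removed; no determinate result is lost |

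The first two rows show redundancy. The next two show assessed patients being deleted. The last is a narrow case in which the exclusion does useful work. A second narrow case arises because the first part of Eligibility asks for any cystoscopy, and only the second part calls it a check: a patient could qualify on a cystoscopy that was not a surveillance visit.

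**3. Effect on the rate.** Let r be the true recurrence among eligible cases, a the share of recurrences removed and b the share of non-recurrences removed. Then

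recorded rate = r(1−a) / [r(1−a) + (1−r)(1−b)].

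All values of r, a and b below are assumptions.

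- r = 15%, a = 10%, b = 0: 0.135/0.985 = 13.7%.
- r = 15%, a = 20%, b = 0: 0.120/0.970 = 12.4%.
- r = 15%, a = 30%, b = 0: 0.105/0.955 = 11.0%.
- r = 15%, a = 5%, b = 10%: 0.1425/0.9075 = 15.7%, so the direction can reverse.
- r = 10%, b = 0, a from 5% to 30%: 9.5% down to 7.2%.
- r = 30%, b = 0, a from 5% to 30%: 28.9% down to 23.1%.
- a = b: the recorded rate equals r.

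**4. Effect on the arm comparison.** Removal multiplies the odds of recurrence in an arm by k = (1−a)/(1−b). The crude odds ratio is therefore multiplied by k(intervention)/k(control).

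- If k is the same in both arms, the crude odds ratio is preserved, although both absolute rates are wrong when a ≠ b.
- If 5% to 30% of recurrences, and no clear results, are removed in the intervention arm alone, a true odds ratio of 1 becomes 0.95 to 0.70.
- If this happens in the control arm alone, it becomes 1/0.95 = 1.05 to 1/0.70 = 1.43.

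The planned model is adjusted and has random effects, so these crude factors are a guide only.

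**The case against.** The best defense is that the wording has a natural, harmless reading. The check cystoscopy is the first follow-up visit after resection, and the exclusion stands directly after one made on resection pathology. On that reading, further surveillance means follow-up after surgery, and the decision precedes the check. The article also condenses a fuller protocol, and the case report forms with their data rules are not shown; the timing of the field may be fixed there.

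Part of this stands. If only decisions made before the check were meant, and those patients then had no cystoscopy, the exclusion changes nothing. But the text does not say so, and the word further fits a decision made after surveillance has begun equally well. Nor is the point about missing detail: Eligibility and Exclusions are both stated, and the fault lies in how they combine.

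A reader might infer that the exclusion can act only on patients whose outcome is known. The two narrow cases in the working show that this goes too far. A reader might also infer that the trial does lose confirmed recurrences, or that the arm comparison is distorted. The documents do not support either. They nowhere say that recurrence makes a patient unsuitable for surveillance, and lack of blinding makes different handling by arm possible without showing it.

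**Conclusion.** The point holds in conditional form. Beyond the eligibility and missing-data rules, the exclusion is either redundant or removes patients who had the in-window cystoscopy, nearly all with a recorded result. Read literally, it allows a recurrence that meets the Assessment definition to be deleted because of a later decision.

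Two conditions govern the harm. The recurrence rate is biased if removal depends on recurrence. The odds ratio between arms is biased only if that dependence differs by arm. The same reasoning applies to the association with the quality indicators, where the dependence would have to differ by indicator status.

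The size cannot be derived from the article, and every percentage for recurrence and removal above is an assumption. The matter concerns the key secondary outcome and its association analyses. It does not touch the coprimary outcomes or the sample size. It merits correction because the ambiguity is easily removed.

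**What to change.** Reconcile Eligibility and Exclusions for early recurrence as follows:

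- Every case with an in-window check cystoscopy and a recorded result under the Assessment definition stays in the analysis, whatever is decided about surveillance before or afterwards. The missing-data and muscle-invasive exclusions remain as they are.
- The surveillance exclusion applies only to patients who have no in-window check cystoscopy, or an indeterminate result, because they were deemed not fit or appropriate for surveillance.
- Use the same term, check cystoscopy, in both parts of Eligibility.
- Report the number excluded for this reason by arm.

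The rule should turn on whether a result exists, not on the date of the decision. A date rule alone would leave unclear what to do with a patient deemed unfit who has the cystoscopy anyway.

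The cost is a few sentences in the outcome definition, one database rule and one line in the patient flow. If the case report form does not already record this reason for exclusion, one field is needed. No extra patients or sites are required. The wording should be settled before database lock and before recurrence is examined by arm.
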